### Assessments

Data on clinical and demographic characteristics (e.g., cancer treatment, race/ethnicity, age, and marital, educational and income status) are collected from cancer registries/medical systems or participants at enrollment. Assessments are conducted occur every 6 months for up to 2 years and include five components: 1) a 2-day dietary recall conducted by telephone [48]; 2) collection of accelerometry-based measures (e.g., physical activity and sleep); 3) anthropometric and physical performance testing; 4) collection of biospecimens, and 5) a phone or online survey. Measures are detailed in Table 2.

**Table 2 Tab2:** Outcomes

**PRIMARY OUTCOMES**	
Diet Quality	Dietary recalls of a non-consecutive weekday and weekend day will be performed via telephone using a multipass method and the Nutrition Data Systems for Research (NDSR) software [48]. The 2-days are averaged at each time point and Diet Quality calculated using the Healthy Eating Index (HEI)-2015, a tool used successfully in a broad range of populations (e.g., minority, older, cancer survivors), [49] will serve as a primary outcome for Project 3 as well as secondary outcomes for Projects 1 & 2, along with other data outcomes, e.g., energy intake and nutrient density.
Objectively-Measured Aerobic Physical Activity	Actigraph accelerometers (Fort Walton, FL) objectively capture physical activity over 7 days and are downloaded and processed using manufacturer procedures and software, and methods similar to those we have reported previously [11]. Moderate-to-vigorous activity assessed using these methods will serve as a primary outcome for Projects 2 and 3, and a secondary outcome for Project 1.
Weight	Measured in light clothing without shoes. The scale dial is captured on Zoom®, first as a “zeroed” value (prior to weighing) and then as the participant weighs. The assessor verifies the weight with both the participant and partner; the process is repeated and the average taken as a primary outcome for Projects 1 and 3 (secondary for Project 2).
**SECONDARY OUTCOMES**	
Other Anthropometric Measures	- Height (self-reported) - Waist circumference: Participant bares midriff to camera and places one end of the ribbon on umbilicus. Partner encircles the waist with the ribbon. The assessor then assures the ribbon is parallel to the floor and flat against the skin as participant rotates in front of camera. Upon exhale, the partner uses a felt-tip marker to mark the ribbon at the point of overlap [50, 51]. The process is repeated with the second ribbon; both ribbons are returned to the study office for measurement and averaging
Physical Performance Testing	The Senior Fitness Battery objectively assesses physical performance in several domains, is sensitive to change, devoid of ceiling effects, and has normative scores [52]. Typically done in-person, tests were adapted to virtual use, refined, and then evaluated for validity and reliability [53]; arm curls and grip strength, were not included given requirements for costly equipment and/or excessive postage. - 30-s chair stand (lower body strength): A standard 18″ unpadded chair is used for this test, though if the participant does not have one, this is recorded and the identical chair is used for follow-up assessments. The participant sits in view of the camera and is instructed to cross arms with hands on shoulders. Upon the assessor’s signal to start, the participant stands up and sits down as many times as possible during a 30-s timed period. - 8′ Get Up & Go test (agility, dynamic balance) Participant starts seated with crossed arms and hands on shoulders while the partner places a sticker and the end of the 8’cord (from mailed supplies) beneath the toe, drawing-out the cord to its full extension in front of the chair. The endpoint is marked by a soccer cone and the cord removed. After positioning the camera to capture the full course and with a focus on the chair (starting and ending points for this test), the participant is given the signal to start. The participant stands up, walks as fast as possible (without running) around the cone, returns to the chair, and sits down. The test is timed using the video – starting from the sign of movement until seated again. - 8′ Walk (gait speed) The chair is removed and the participant starts standing with their toe on the sticker (see test above). Upon the signal to start, they walk as fast as possible through the 8′ point marked by 2 soccer cones (another cone is used to increase visualization) and the camera is focused on the finish-line. This test also is timed using the video – starting from the sign of movement until the finish line is crossed. - Sit-and-reach (flexibility) Seated on the edge of the chair, the participant extends one leg so heel remains on floor, the knee is fully extended and the toe pointed to the ceiling. With the camera capturing the side view of the participant, they are instructed to overlap their hands and extend them towards the toe. The partner measures the distance from the middle finger to the big toe with a vinyl tape measure. Positive for over-reach, negative for under-reaching, zero for touching. - Back scratch (flexibility) While standing with their back toward the camera, the participant reaches arm out and over same shoulder, reaches other arm directly back and attempts to clasp other hand. The partner measures the distance between closest fingers (scoring identical to the test above). - 2-min step test (endurance) The partner is instructed to palpate the participant to locate the iliac crest and then uses the vinyl tape measure to record the distance to the top of the patella which is called-out to the assessor. The assessor calculates the midpoint which is denoted by a sticker. The partner is then asked to measure the distance from the sticker to the floor and call-out the value to the assessor. The assessor records this value for future testing and then instructs the partner to measure this distance against a wall and to mark it with another sticker. Upon the command to start, the participant “marches in place” for 2 min making sure to bring their knees up to point of the sticker. The participant is instructed not to talk, and to take breaks and steady themselves against the wall should they need to while timer continues (the partner also is instructed to “spot” the participant as needed). The number of steps reaching the mark are counted.
Balance Testing	Side-by-side, semi-tandem and tandem stance balance testing as per the Centers for Disease Control protocol is captured on Zoom® [54]. To reduce ceiling effects, the latter test is extended for up to 2 min (or until the stance is broken). This test is also performed near a wall should the participant need to steady themselves.
Blood Pressure	Participant is instructed to sit quietly in front of the camera for 5 min (during which time the assessor turns-off the Zoom® video). Once resumed, the partner is instructed to place the cuff of the automated sphygmomanometer on the participant and to press start (making sure the camera is focused on the display). The assessor reads the values and verifies them with the partner. Blood pressure is standardly assessed in the upper right arm, unless there are contraindications, such as surgery or radiation therapy on the right side; left side assessments are noted and repeated for follow-up assessments.
Muscle Mass	As in the Osteoporotic Fractures in Men (*MrOS*) *Study,* the deuterium creatine (D_3_Cr) dilution method is used that capitalizes on a stable, non-radioactive isotope, to assess muscle mass remotely [55–57]. Participants are provided with a 30 mg capsule of D3Cr and instructed to take the capsule 3 days prior to their assessment date. The night prior to assessment, they begin fasting and continue fasting until they produce the second urinary void of the day. During this void, a test strip is used. The strip is frozen (0 C^o^ or below) until analyzed, using methods originally reported by Clark et al. and adapted by Evans et al. [55–57].
Circulating Biomarkers^a^	Assessor guides the participant in obtaining 5 blood spots on a designated card, which is then dried thoroughly, inserted into a foil pouch with desiccant and frozen (0 C^o^ or below) until analyzed. DBS eluents are batch-tested against known standards for Thyroid Stimulating Hormone (TSH), insulin, glucose, leptin, adiponectin, high density lipoprotein and total cholesterol, triglycerides, interleukin-6, c-reactive protein and tumor necrosis factor alpha at the University of Washington as described previously [58]. Values are expressed in plasma equivalent terms.
Patient Reported Outcomes^a^	*Physical Activity:* As accelerometry provides only activity counts, two common instruments are used to capture data on the various types of physical activities the participants engage in: 1) Godin Leisure-Time Exercise Questionnaire (GLTEQ) is administered given its ease of use and excellent reliability and validity in cancer survivors [59]. An updated version that includes frequency and average minutes of duration of exercise/week within intensity categories (strenuous, moderate [including strength training] and mild) was selected for the current study [60]; and 2) Global Physical Activity Questionnaire (GPAQ) is a 16-item instrument developed for the World Health Organization that assesses physical activity within the contexts of recreation, work and travel. It also measures sedentary behavior and has proven validity and reliability across a broad spectrum of populations [61]. *Cancer-related Outcomes:* The PROMIS Cancer-Related Item Bank is used to assess global physical, mental and social health, perceived stress, and QOL in specific domains, i.e., depression, anxiety, fatigue, sleep, and pain [62]. This tool was synthesized from previous QoL instruments (FACT, EORTC, etc.) and relies on item response theory and complex algorithms to pinpoint the most relevant items in each domain, while reducing the number of items assessed (patient burden). This measure will be completed over the phone or self-administered online, as in past studies [63]. *Quality of Life:* QOL will be measured with the PROMIS global health scale and the EuroQOL-5D-5L (EQ-5D-5L) The EQ-5D-5L assesses 5 dimensions (Mobility, Self-care, Pain/Discomfort, and Anxiety/Depression) [64] at 5 levels of severity: its scores of this instrument are used to calculate Quality Adjusted Life Years. *Health Care Utilization* the validated instrument of Ritter et al. has test-retest reliability of 0.76–0.97 and will capture physician and emergency room visits, and hospitalizations [65], and will be amended to include out-of-pocket costs related to medical visits, and costs of prescribed and over the counter medications [66]. *Comorbidity:* The Older Americans Resources & Services (OARS) Comorbidity Index (43-items) used in multiple studies in older adults will assess the number of chronic medical conditions and symptoms and their functional impact (severity). In addition to serving as an outcome, comorbidity at baseline will be evaluated as a potential moderator. Since falls are a particular issue in this population, an item validated by Chen & Janke that assesses falls in the past year also will be included [67].

^a^Some assessment components (e.g., the Global Physical Activity Questionnaire and biomarkers) were added because of the opportunity to participate in the Accumulating Data to Optimally Predict Obesity Treatment (ADOPT) Consortium [68]

Though almost all AMPLIFI participants complete the anthropometric and physical performance tests over Zoom®, some participants may complete assessments in-person if within driving distance of UAB. Remote assessments are scheduled with each participant; prior to the appointment, they receive the following supplies: 1) Automated sphygmomanometer (Omron 3 Wrist Blood Pressure Monitor, Omron Healthcare Inc., Lake Forrest, IL) to measure blood pressure (an appropriately-sized cuff also is provided based on weight status); 2) Actigraph® accelerometer wGT3X-BT (Pensacola, FL) with an activity/sleep log; 3) One 30 mg capsule of D3 creatine, a urine test strip, and instructions to assess muscle mass; 4) A dried blood spot (DBS) kit (collection card, 2 lancets, band-aid, foil storage pouch, and desiccant) to self-collect a blood sample; 5) Two ribbons (55″ × 1″) and a felt-tip marker (to measure-and-mark waist circumference in duplicate); 6) An 8′ length of cord and two stickers (to mark the distance for the 8′ walk and up-and-go performance tests); 7) two plastic orange soccer cones (to increase visualization of distance-walked on virtual assessments); and 8) a 36″ vinyl tape measure and one sticker (to measure step height for 2-min step test). Also, for participants not owning a scale, a digital scale is included. Prior to the visit, participants and their assessment partners are asked to view instructional videos on performance tests developed by the AMPLIFI team (https://youtu.be/lbxctNuOgLk), collection of DBS (https://youtu.be/lBPLS4PoHv4) and D3 creatinine (https://youtu.be/6BpUgdnPh1c).

Virtual protocols were assessed for reliability and validity, and assessors were trained and evaluated for accuracy prior to initiation [53]. Zoom® sessions are recorded to permit accuracy for timed performance testing, reduce the discrepancy introduced by differential transmission of sight and sound and inform periodic quality assurance evaluations among assessors. Once assessors review these files, time the tests, and log the data, and quality assurance tests are completed, the recordings are deleted. The assessment is repeated in the same modality every 6 months.

The assessment survey is designed to collect secondary patient-reported outcomes (Table 2) and the mediators of intervention effects. As Social Cognitive Theory (SCT) provides the behavioral theory framework for the AMPLIFI interventions [19] (Fig. 2), key constructs of SCT are measured at assessment points (baseline, 6, 12, and 18 months). Constructs include: 1) Self-efficacy: The 20-item diet-related instrument (specified in relation to high calorie foods) of Clark et al. [69] and the walking (task) self-efficacy scale of McAuley et al. [70] (abbreviated to 5 items ranging from confidence in walking 10, 20, 30, 40, or 50 min) are used given excellent internal consistency (α = 0.70–0.95) and validated use in cancer survivors. In addition, the 8-item barriers self-efficacy scale for aerobic exercise [71] is used and adapted to include 7-items for resistance exercise; 2) Social support: The validated 5-point scales for exercise and eating a healthy low calorie diet from Sallis et al. [72] which have acceptable test-retest reliabilities (r = 0.55–0.86) and internal consistencies (α = 0.61–0.91) are also employed; and 3) Common barriers to exercise (21 items), resistance training (11 items), and low calorie foods (10 items) are assessed using 5-point Likert-scaled instruments [34, 36, 73, 74].

**Fig. 2 Fig2:**
[figure not shown]
Conceptual model

Questions on health events, falls, and health care utilization are included at each assessment time point as well as midway between assessments (i.e., every 3 months). This information is used to assess potential adverse events. Participants are also asked to report any adverse events immediately to the team using the toll-free study number or study email address. At completion of the intervention, telephone debriefings are performed to capture program satisfaction and solicit suggestions for improvement.

### Randomization

After completion of the baseline assessment, and using a fixed block design, all participants (*n* = 652) are randomized to the sequenced (*n* = 326) or the wait-listed/simultaneous intervention arms (*n* = 326). Sequenced arm participants are then immediately randomized to diet or exercise intervention sequences (*N* = 163 each) for projects 1 and 2. The study flow is depicted in in Fig. 1. The randomization sequence was generated using SAS (Version 9.4, Cary, NC) by an off-site biostatistician. Arm assignment is managed by a central office of blinded staff who have no contact with study participants and implement the computer-generated randomization sequence as baseline assessments are completed.

Participants who are randomized to the wait-list control (followed by the simultaneous intervention), receive brief monthly modules on survivorship topics during the 6-month period they are wait-listed. These modules use the same web-based platform as the other AMPLIFY interventions. Topics are: 1) Good Communication with Physicians; 2) Importance of Quality Sleep; 3) Cognitive Functioning; 4) Benefits of Laughter; 5) Benefits of Creative Arts; and 6) Welcome to the AMPLIFY diet and exercise intervention. This last module serves as an introduction to the simultaneous intervention and addresses next steps and expectations.

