## Methods/design

### Overview

The three AMPLIFI projects include two 6-month RCTs testing diet (project 1) or exercise (project 2) interventions versus a wait-list control condition. After 6 months, diet and exercise arm participants progress to the next behavioral intervention sequence and the wait-list arm begins a 12-month combined diet and exercise intervention. Project 3 will examine data from all participants to determine the relative efficacy of the 12-month diet and exercise intervention when presented sequentially versus simultaneously to cancer survivors (Fig. 1).

Under the AMPLIFI umbrella, the three RCTs maximize economies of scale by instituting identical eligibility criteria and protocols for accrual, identical intervention design elements and outsourcing, as well as identical protocols for assessment and outcomes. Like the vast majority of behavioral intervention trials, AMPLIFI RCTs are single-blinded; assessments are performed at baseline and every 6 months by assessors who are masked to randomization status with each RCT’s primary endpoint assessed upon intervention completion and durability assessed 6 months thereafter. The three RCTs are interwoven to maximize the contribution of wait-list controls, and ability to answer the overarching research question of sequenced versus simultaneous delivery of exercise and dietary components (Fig. 1).

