### Retention

Retention is addressed at the participant, researcher, and contextual levels [75]. At the participant level, a series of communications was developed to convey appreciation for participation in the trial, e.g., e-cards with brief appreciation videos from investigators at regular intervals, birthday e-cards, and mailed Happy New Year cards. The AMPLIFY logo was incorporated into the design of all communications to ensure easy recognition by participants. At the contextual level, a tracking system shared by assessors and recruiters (who also schedule follow-up assessments) was developed to ensure consistent communication with each participant. At the researcher level, investigators ([name]), recruiters, assessors, and project managers, meet weekly to review recruitment and retention numbers to ensure that participants at risk of drop-out are identified early. Changes to procedures and communications with participants are discussed at these meetings to ease participant burden and reduce drop-out risk. Participants who may need to pause the intervention due to health or personal reasons (e.g., COVID-19, elected/emergency surgeries, deaths in the family, changes of residence, prolonged vacations) are also discussed by project managers and investigators ([name]) to determine when they can resume participation. Outcome data will be collected from all participants, including those who discontinue or deviate from the intervention protocols and are still willing to participate in assessments.

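### Fixed-size blocks leave a small, avoidable risk that staff who know earlier assignments could predict the end of a block; randomly varied, undisclosed sizes would remove most of it

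*Protocol article*

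**What the plan says.** The Randomization section of the protocol article sets out two stages. First, "After completion of the baseline assessment, and using a fixed block design, all participants" (652) are split 326 to the sequenced arm and 326 to the wait-list/simultaneous arm. Then "Sequenced arm participants are then immediately randomized to diet or exercise intervention sequences", 163 to each. No strata are named and no block size is given.

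The same section describes the safeguards. "The randomization sequence was generated using SAS (Version 9.4, Cary, NC) by an off-site biostatistician", and "Arm assignment is managed by a central office of blinded staff who have no contact with study participants". These staff "implement the computer-generated randomization sequence as baseline assessments are completed".

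The Overview adds: "AMPLIFI RCTs are single-blinded; assessments are performed at baseline and every 6 months by assessors who are masked to randomization status". Masking is stated there for assessors. The article does not state it for recruiters, project managers or investigators, and participants necessarily know which programme they receive.

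The Retention section says that investigators, "recruiters, assessors, and project managers, meet weekly to review recruitment and retention numbers". It also describes a tracking system used by both assessors and recruiters, and says that project managers and investigators discuss participants who need to pause the intervention. Whether arm is visible in the meetings or in the system is not stated.

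**The concern.** Central holding of the list hides future assignments. It does not by itself prevent prediction from past ones. With one constant block size, a person who knows the earlier assignments in order can work out that size, and then knows the last assignment or assignments of each block. Recruiters or staff who schedule baselines, if they had that knowledge, could hurry, delay or encourage particular people.

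All three projects draw on the same first-stage allocation. Their binary goals (3% weight loss, 150 weekly minutes of activity, better diet quality) plausibly depend on motivation, so selective placement could create a difference between arms without any intervention effect. Analysis cannot fully repair that afterwards. Because the trial is still recruiting and allocation is already running, a later analysis plan would not address it either.

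**Working it through.** **1. The plan's own numbers.** With 20% drop-out, 520/0.8 = 650, 260/0.8 = 325 and 130/0.8 = 162.5, rounded up to 163. Then 2 × 163 = 326 and 2 × 326 = 652. The randomised totals reproduce, and this point disputes none of them.

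**2. Assumption.** The block size is unknown, so sizes 2 to 8 are shown. The guesser is assumed to know the size and every earlier assignment. This is the worst case.

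**3. Assignments known with certainty.** In a 1:1 block of size b the share is 1/(b/2 + 1). Check for b = 4: the six orders AABB, ABAB, ABBA and their mirror images have 2, 1 and 1 forced places, so 2 × (2 + 1 + 1)/(6 × 4) = 8/24 = 1/3.

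**4. Correct guesses (always guessing the lagging arm).** For b = 4 the four places give 1/2, 2/3, 2/3 and 1, so 2.833/4 = 70.8%.

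| Fixed size | Certain | Of 652 | Correct guesses |
|---|---|---|---|
| 2 | 50.0% | 326 | 75.0% |
| 4 | 33.3% | 217 | 70.8% |
| 6 | 25.0% | 163 | 68.3% |
| 8 | 20.0% | 130 | 66.6% |

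**5. Delayed information.** If the guesser is one assignment behind at b = 4, the places give 1/2, 1/2, 2/3 and 2/3, so 2.333/4 = 58.3% correct. Only the fourth place can be certain, with probability 1/3, so 1/12 = 8.3%. Two behind gives 0% certain and 54.2% correct. At b = 8, one behind gives 7.5% certain and 60.4% correct.

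**6. Effect on the tests.** Suppose b = 4, favoured participants have a success rate 10 points higher (an assumption), and every placement follows the guess. The share of favoured participants then differs between arms by 2 × 0.708 − 1 = 0.42, so the arms differ by about 4.2 points with no intervention effect. The Sample size section plans for differences of 16.6, 13.8 and 11.1 points.

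- Project 3 (260 per arm, base 22.2%): SE = √(0.243 × 0.757 × 2/260) = 0.0376. The shift is 0.0417/0.0376 = 1.11 SE, and the two-sided rejection rate is about 20%.
- Project 1 (130 against 260, base 27.3%): the same calculation gives about 14%.
- If only a quarter of placements are steered, the difference is 4.2/4 ≈ 1.0 point and the rates are 5.9% and 5.6%, against a nominal 5%.

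**7. What varying the sizes buys (guesser with full knowledge of the past).**

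| Scheme | Certain | Correct guesses |
|---|---|---|
| Fixed 4 | 33.3% | 70.8% |
| Fixed 6 | 25.0% | 68.3% |
| Random 4/6/8 | 2.3% | 68.1% |
| Fixed 12 | 14.3% | 64.3% |

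Random sizes remove nearly all certain predictions. At the same average size (6) they hardly change the rate of correct guesses. That rate falls with larger blocks: random 8 to 16 gives 64.3%, the same as fixed 12.

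**The case against.** A reader might infer that one small remote team watches running arm counts, so that assignments can be inferred and baselines timed to suit. The article does not support that. The Abstract calls the project multi-site, and the Overview describes four shared resources. The weekly meetings are said to cover recruitment and retention figures, not allocations. Nothing says that recruiters or assessors see assignments in order or know the block size. Assessors, who carry out the baselines, are masked. Leaving the block size out of a published article is sound practice, and strata may be given in the full protocol.

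Steering would also be hard in practice. According to Table 2 and the Assessments section, a baseline needs recalls on two non-consecutive days, seven days of accelerometry, a capsule taken three days beforehand, mailed supplies and a partner at a scheduled session. With concurrent accrual nationwide, completion order depends heavily on participants and logistics. The motive is weaker than in many wait-list trials, because every participant is eventually offered both programmes.

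All of this stands, and it makes the point minor. What survives is narrower. These safeguards hide the list, but the article does not say that recruiters, project managers and investigators are kept from past assignments, and a constant size can be deduced without being disclosed. The Overview also gives one shared resource both the baseline assessments and the implementation of the randomisation scheme, without saying how this fits with the separate central office.

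**Conclusion.** The point holds as a precaution. A fixed block design is stated, participants are not blinded, and the described concealment does not exclude prediction by unmasked staff who know earlier assignments. The upper bound is 20% to 33% of assignments certain, if the block size is between 4 and 8 and the guesser has complete and immediate knowledge. It falls to about 8% with information one assignment behind (size 4 or 8). The 20% and 14% false-positive rates also need every placement to be steered and a 10-point prognostic gap; about 6% is the figure if a quarter are steered.

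The article does not show that anyone has inferred or steered assignments. No sample size, power or significance level changes.

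**What to change.** For participants still to be randomised, have the off-site biostatistician regenerate both stages of the list with randomly varying block sizes, starting at a block boundary and run by the same central office. In the Randomization section, replace the fixed block wording with: *randomly permuted blocks of varying size, with the sizes withheld from all recruiting, assessing and intervention staff.* Add a sentence on how the Assessment and Analysis resource relates to the central office. If fewer correct guesses overall are also wanted, the sizes must be larger, for example drawn from 8 to 16.

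The cost is one new list and a short protocol change, with no new staff or system. The downside is a slightly larger possible imbalance when accrual ends inside a block: at most half the largest block, so 4 participants with sizes up to 8, or 8 with sizes up to 16, against 2 with fixed 4.
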